## Abstract

**Background:**

The advantages of laparoscopic left-sided hepatectomy (LLH) for treating hepatolithiasis in terms of the time to postoperative length of hospital stay (LOS), morbidity, long-term abdominal wall hernias, hospital costs, residual stone rate, and recurrence of calculus have not been confirmed by a randomized controlled trial. The aim of this trial is to compare the safety and effectiveness of LLH with open left-sided hepatectomy (OLH) for the treatment of hepatolithiasis.

**Methods:**

Patients with hepatolithiasis eligible for left-sided hepatectomy will be recruited. The experimental design will produce two randomized arms (laparoscopic and open hepatectomy) at a 1:1 ratio and a prospective registry. All patients will undergo surgery in the setting of an enhanced recovery after surgery (ERAS) programme. The prospective registry will be based on patients who cannot be randomized because of the explicit treatment preference of the patient or surgeon or because of ineligibility (not meeting the inclusion and exclusion criteria) for randomization in this trial. The primary outcome is the LOS. The secondary outcomes are percentage readmission, morbidity, mortality, hospital costs, long-term incidence of incisional hernias, residual stone rate, and recurrence of calculus. It will be assumed that, in patients undergoing LLH, the length of hospital stay will be reduced by 1 day. A sample size of 86 patients in each randomization arm has been calculated as sufficient to detect a 1-day reduction in LOS [90% power and *α* = 0.05 (two-tailed)]. The trial is a randomized controlled trial that will provide evidence for the merits of laparoscopic surgery in patients undergoing liver resection within an ERAS programme.

**Conclusions:**

Although the outcomes of LLH have been proven to be comparable to those of OLH in retrospective studies, the use of LLH remains restricted, partly due to the lack of short- and long-term informative RCTs pertaining to patients with hepatolithiasis in ERAS programmes. To evaluate the surgical and long-term outcomes of LLH, we will perform a prospective RCT to compare LLH with OLH for hepatolithiasis within an ERAS programme.

**Trial registration:**

ClinicalTrials.gov NCT03958825. Registered on 21 May 2019.

**Supplementary Information:**

The online version contains supplementary material available at 10.1186/s13063-023-07476-w.

## Background

Hepatolithiasis is defined as a gallstone disease in the intrahepatic bile ducts and is mainly prevalent in Southeast Asia [1]. Hepatolithiasis may occur alone or with extrahepatic bile duct stones. Long-term hepatolithiasis can cause secondary biliary stricture, liver cirrhosis, and even cholangiocarcinoma [2]. Hepatectomy is one of the most effective methods for treating intrahepatic stones because it can simultaneously remove stones and relieve bile duct stricture [3, 4]. For hepatectomy of hepatolithiasis, due to the presence of stones in the left liver of most patients with intrahepatic bile duct stones, left hepatectomy, including left lateral hepatectomy and left hepatectomy, is the most common procedure performed. With the advancement of laparoscopic technology, laparoscopic liver resection has been used in the treatment of various liver diseases, including benign and malignant liver tumours [5, 6]. Since Louisville’s statement in 2008, the international status of laparoscopic hepatectomy has been widely recognized [7]. However, laparoscopic hepatectomy in patients with hepatolithiasis may be more difficult and challenging than open hepatectomy because patients with hepatolithiasis usually experience changes in their normal anatomy and perihepatic adhesion due to chronic inflammation [8–10]. To date, only a few retrospective studies have compared the outcomes of laparoscopic left-sided hepatectomy (LLH) with those of open left-sided hepatectomy (OLH) for hepatolithiasis, and the feasibility and efficacy of LLH have not been fully evaluated [11, 12].

Enhanced recovery after surgery (ERAS) programmes have been applied for patients receiving small-scale and large-scale liver resection [13, 14]. Several studies have shown that ERAS programmes are safe, feasible, and effective in reducing the median LOS in both open and laparoscopic resection [15, 16]. In some retrospective trials comparing earlier recovery or a reduction in LOS, perioperative evaluation or management has not been uniform [12, 17]. In addition, the value of laparoscopic left-sided hepatectomy for hepatolithiasis compared with that of open left-sided hepatectomy within an ERAS programme in terms of LOS and hospital costs has not been studied in a randomized controlled trial (RCT). However, randomized grouping of patients undergoing open or laparoscopic liver resection is dangerous. Due to the lack of clinical and patient equipoise of laparoscopic surgery, experienced centres and surgeons are reluctant to randomize patients. To take advantage of two centres’ preferences and disapproval of laparoscopic liver surgery to obtain a series of uninterrupted prospective patients, we constructed a randomized controlled trial design with two randomized groups (open and laparoscopic surgery) and a prospective registry. Combining an RCT with a prospective registry will improve the overall power and enhance the external validity and generalizability of the study results [18].

The day of discharge from the hospital is dependent on multiple factors, including patient expectations, local discharge logistics, cultural differences between countries, hospitals, and surgeons. LOS may therefore be considered an inappropriate endpoint for comparison of surgical interventions. Within the ERAS programme for liver surgery, a composite endpoint has been defined: time to functional recovery [15]. This endpoint, representing medical readiness for discharge, consists of clear and objectively measurable criteria. A patient is considered functionally recovered if they have a normal or decreasing serum bilirubin level, good pain control with oral analgesia only, tolerance of solid food, no intravenous fluid support, and independent mobility at the preoperative level [15]. Functionally recovered patients are generally capable of performing activities of daily living independently and are independent of hospital care. Therefore, we will conduct this randomized controlled trial to evaluate the safety and effectiveness of LLH for hepatolithiasis by comparing its clinical outcomes with those of OLH.

## Methods

### Design

A randomized clinical trial and a prospective registry with two parallel groups will be conducted at the General Surgery Department of the Second Affiliated Hospital of Anhui Medical University in China. The aim of this study is to compare the effect of two hepatectomy methods for hepatolithiasis by assessing factors related to mortality and morbidity, including the length of postoperative hospital stay (LOS), biliary leakage [19], posthepatectomy haemorrhage [20], posthepatectomy liver failure [21], incisional hernias, residual stone rate, and recurrence of calculus [22].

### Study population

Adult patients with an indication for elective left lateral sectionectomy and left hemihepatectomy because of left intrahepatic bile duct stones with irreversible disease, such as biliary strictures, severe parenchymal fibrosis, or atrophy.

### Inclusion criteria

To be eligible to participate in this study, a patient must meet all of the following criteria:Patients suitable for undergoing both laparoscopic left hepatectomy and open left hepatectomy of the liverPatients who can understand the nature of the study and its requirementsMen and nonpregnant, nonlactating women between the ages of 18 and 80Patients with ASA I-II-III

### Exclusion criteria

Patients who meet any of the following criteria will be excluded from participation in this study:Inability to provide informed consentPatients associated with a tumour or who require bilioenteric anastomosis or left caudate lobectomyImmunodeficiency diseases, such as HIVPrevious upper abdominal surgery (except for laparoscopic and open cholecystectomy)

### Randomization

Patient recruitment and the collection of written informed consent will be performed at the outpatient clinic. Patients will be randomized to the different groups using the block randomization method. Each block contains two groups: the OLH group and the LLH group. The block size will be hidden from the trial executors and clinicians. Possible balanced combinations of these groups within the block will be numbered consecutively. Then, blocks will be randomly chosen using the ‘randomize’ library of SPSS 22.0 (SPSS, Chicago, USA), and a series of randomly assigned OLHs and LLHs will be generated based on the random sequence of blocks. Allocation will be concealed using sequentially numbered, sealed opaque envelopes prepared by a member of our Clinical Trial Center. Patients will be randomly allocated to either OLH or LLH before surgery. The trial executors will receive randomly generated treatment allocations within sealed opaque envelopes. Afterwards, medical staff will personally inform the expert surgeon as to which treatment group the patient has been randomized. To avoid any potential prediction of group allocation, information on the block length will be kept away from the study site.

### Assignment of interventions: allocation

#### Sequence generation

A randomization table will be made by using the ‘randomize’ library of SPSS 22.0 (SPSS, Chicago, USA). The table will be managed by one staff member who is a doctor but not associated with this trial.

#### Allocation concealment mechanism

Eligible patients will be allocated to receive the designated intervention during the operation. However, they will get to know their allocation after POD3. On the other hand, the operator will be unblinded just before surgery to conduct the appropriate intervention for the patient.

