### Blinding

In this trial, all assessors of the primary outcome (i.e. the ward doctor), the patients, and the adjudication committee will be blinded to the operation allocation. Directly after skin closure, while still under general anaesthesia, patients will receive a firmly taped, large 40 × 40 cm abdominal dressing to cover their incision(s) and therefore their treatment allocation (minimally invasive or open). This abdominal dressing will be removed when all criteria for functional recovery are met or earlier for medical reasons, such as suspicion of wound infection. If an earlier inspection is needed, attempts will be made to maintain patient blinding.

The success of blinding will be assessed using the blinding index as proposed by Bang et al. [23]. Both patients and ward doctors will be asked about the alleged treatment allocation based on five categories: (1) strongly believe it was LLH, (2) somewhat believe it was LLH, (3) somewhat believe it was OLH, (4) strongly believe it was OLH, and (5) do not know. Sensitivity analysis will be performed for the analysis of time to functional recovery.

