### Type of trial

The trial is a prospective randomized interventional single-centre study comparing two parallel groups with a prospective registry to determine whether patients underwent LLS by laparoscopic surgery rather than open surgery with an enhanced recovery programme. The types of interventions by patients, nurses, and ward doctors (not the surgeons performing the operations) before postoperative day (POD) 3 will be blinded. However, patients who are randomized to receive open or laparoscopic liver resection are at risk, as explained earlier. In addition, there is another potential source of bias when randomly selecting patients with strong treatment preferences. When patients are not informed about their treatment allocation (POD 3), they may be resentful and feel demoralized if they do not receive their preferred treatment. Thus, their compliance may be poor. In contrast, patients receiving their preferred treatment may have above-average compliance. Thus, to capitalize on centres both with and without preference for laparoscopic liver surgery and to acquire an uninterrupted prospective series of patients, all nonrandomized patients undergoing LLS will be approached to participate in the prospective registry. Registration of these patients is imperative to guarantee a consecutive series of patients and because the absence of such a series may restrict the generalization of the results, as randomized participants may not, in fact, be representative [24].

Nonrandomized patients will be asked for permission to use their data. In doing so, they will be assigned to the OLH or LLH group of the prospective registry on the basis that this registry might increase the external validity of results obtained in the randomized study [15, 18, 25].

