### Primary endpoint

The primary outcome of this trial is the LOS. Only the researchers and surgical surgeons will know the true operation. A blinded ward doctor will decide whether the patient should be discharged.

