### Statistical aspects

#### Sample size calculation

The sample size calculation is based on the primary endpoint: the LOS. According to published data, an assumed 1-day reduction in LOS is the appropriate basis for the calculation, assuming 5 days in the LLH group and 6 days in the OLH group [28]. This calculation yields a total of 86 patients in each group, which assures 90% power at a two-sided level of significance of 5% [NCSS and PASS 15 (NCSS Statistical Software, Kaysville, UT, USA)]. Assuming an expected withdrawal rate of 10% during the trial, 18 additional patients will be included and randomized; therefore, the total sample size required is *n* = 190 patients (Fig. 3).

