## Discussion

The left side of the liver is a common site for and is more seriously affected by hepatolithiasis. Hepatectomy has been the most effective treatment for removing IHD stones and resolving bile duct strictures, thereby decreasing the risk of recurrence [3, 22]. Compared with open hepatectomy, laparoscopic hepatectomy enables more accurate visualization and vascular anatomy. However, only a few retrospective studies comparing OLH and LLH without the ERAS programme have summarized the complications and long-term follow-up dates, such as residual stones and risk of recurrence, which are the main concerns of surgeons [11, 12].

The present study is the first RCT to compare the benefits of the laparoscopic approach to left-sided hepatolithiasis in Chinese patients undergoing hepatectomy with the ERAS programme. It is well recognized that a well-conducted double-blind RCT provides the highest level of evidence to prove the possible benefits of laparoscopic liver resection. However, performing an RCT during surgery is not without difficulties, and alternative trial designs may be necessary [25, 28]. First, the intervention needs to be tested in a standardized environment, and the properties of the intervention should remain unchanged during the trial period. The surgeons should have advanced laparoscopic experience and open liver resection experience. Both the LLS and the ERAS programme-enhanced recovery protocol provide the standardization needed. Second, the intervention should be double-blinded. Although double blinding in a surgical trial is difficult, using a fixed abdominal dressing for 3 days after surgery is feasible and should prevent both ward caregivers and patients from knowing the type of intervention. The trial with randomization of patients and surgeons with treatment equipoise and a prospective registry to cover both surgeons who believe that, based on their laparoscopic experience, randomization is not ethically justified and patients with a strong treatment preference will provide external validity. This trial design, which capitalizes on rather than ignores the differences between patients, will provide more robust outcome data and should lead to continuous performance monitoring after the trial.

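### The article gives conflicting end-points for the blind (POD 3, functional recovery, discharge), and the POD 3 statements would leave most length-of-stay decisions unprotected

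*Protocol article*

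**What the plan says.** Three places in the protocol article tie the end of the blind to about postoperative day 3:

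- Allocation concealment mechanism, on patients: "However, they will get to know their allocation after POD3".
- Type of trial: "The types of interventions by patients, nurses, and ward doctors (not the surgeons performing the operations) before postoperative day (POD) 3 will be blinded".
- Discussion, on double blinding of ward caregivers and patients: "using a fixed abdominal dressing for 3 days after surgery is feasible".

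Two places promise more:

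- Blinding names the ward doctor as assessor of the primary outcome, says that this doctor and the patients are blinded, and states: "This abdominal dressing will be removed when all criteria for functional recovery are met or earlier for medical reasons".
- Primary endpoint: "A blinded ward doctor will decide whether the patient should be discharged".

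The primary outcome is LOS, which Table 1 counts from the day of operation to discharge. Sample size calculation plans it by "assuming 5 days in the LLH group and 6 days in the OLH group". Blinding also says: "Sensitivity analysis will be performed for the analysis of time to functional recovery". It names no such analysis for LOS.

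**The concern.** A site cannot follow all of these statements as written. If ward doctors are blinded only before POD 3, a discharge decision on day 5 or 6 is not made by a blinded ward doctor.

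The conflict falls on the primary outcome, and the article explains why that matters. Its Background says that the day of discharge depends on patient expectations and local logistics, among other factors, and that LOS may for this reason be considered an inappropriate endpoint. Type of trial adds that patients with strong preferences may comply better or worse according to whether they received the preferred operation. Masking is the main protection offered for a partly discretionary endpoint. If it ends before discharge, expectations of faster recovery after laparoscopy could contribute to an observed difference, and the data could not separate that contribution from a true effect.

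**Working it through.** **1. When each statement ends the blind**

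| Section | Who is covered | End of the blind |
|---|---|---|
| Allocation concealment mechanism | patients | some time after POD 3, no day fixed |
| Type of trial | patients, nurses, ward doctors | blinded before POD 3 |
| Discussion | ward caregivers, patients | 3-day dressing |
| Blinding | ward doctor, patients, adjudication committee | functional recovery, or earlier for medical reasons |
| Primary endpoint | ward doctor | still blinded at the discharge decision |

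Type of trial and Primary endpoint conflict directly on the ward doctor for any discharge on POD 3 or later. The Discussion and Blinding conflict on the dressing for any patient not functionally recovered by day 3. Even Blinding alone does not reach the endpoint: the dressing comes off at functional recovery, and discharge may follow later.

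**2. Where discharge falls**

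The planned means are 5 days (laparoscopic, LLH) and 6 days (open, OLH). They lie 5 − 3 = 2 and 6 − 3 = 3 days past POD 3. The Discussion's worldwide range of median stays, 4 to 8 days, also lies wholly past POD 3. This step needs no SD.

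**3. The SD implied by the sample size**

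The article gives 86 per arm, a difference of 1 day, 90% power and two-sided 5%, but no SD. From n = 2·SD²·(1.960 + 1.282)²/1², SD = √(86/2)/3.242 = 2.02. As a check, SD = 2.0 in a two-sample t-test needs 85.03 per arm, rounded up to 86. The planned number is therefore consistent with an SD of about 2, which is an inference.

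**4. Share of discharges after POD 3**

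P(LOS > 3) with the planned means, under three assumed shapes:

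| SD | Shape | LLH | OLH | Pooled 1:1 |
|---|---|---|---|---|
| 1 | normal | 97.7% | 99.9% | 98.8% |
| 1 | gamma | 98.9% | 100.0% | 99.4% |
| 1 | lognormal | 99.3% | 100.0% | 99.6% |
| 2 | normal | 84.1% | 93.3% | 88.7% |
| 2 | gamma | 85.0% | 96.0% | 90.5% |
| 2 | lognormal | 87.1% | 97.6% | 92.3% |
| 3 | normal | 74.8% | 84.1% | 79.4% |
| 3 | gamma | 71.8% | 85.7% | 78.7% |
| 3 | lognormal | 74.0% | 89.1% | 81.6% |

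With a stricter cut at 3.5 days (discharge on day 4 or later), the pooled share is 83% to 85% at SD 2 and 72% to 74% at SD 3. Over all these cases it runs from 72% to 99.6%. The lowest single-arm value is 64% (LLH, SD 3, gamma, 3.5-day cut).

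**5. What a small expectation effect could do (illustration only)**

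With SD 2, the standard error of the difference is 2·√(2/86) = 0.305 day. Suppose there is no true effect, but knowledge of allocation shifts mean LOS by b. The two-sided rejection probability is Φ(b/0.305 − 1.960) + Φ(−b/0.305 − 1.960):

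- b = 0.3 day: about 17% instead of 5%
- b = 0.5 day: about 37% instead of 5%

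Nothing in the article supports or excludes shifts of this size.

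**The case against.** The sections devoted to the matter, Blinding and Primary endpoint, both promise a blinded ward doctor. A reader might infer from the POD 3 wording that allocation is disclosed on that day and that most LOS values are in fact decided unblinded. The documents do not support so firm a reading:

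- The sentence under Allocation concealment mechanism concerns patients only. It sets an earliest time, not a day, so disclosure at functional recovery or at discharge would also comply with it.
- The Discussion sentence argues that a 3-day dressing is feasible. It is not an operating rule.
- Only Type of trial limits ward-doctor blinding to the time before POD 3, and its wording is garbled.

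Discretion may also be narrower than the Background suggests. The trial has one centre, uses a standardised ERAS programme and defines functional recovery by explicit criteria. The SD and the bias sizes used above are not the article's.

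All of this stands, and it limits the point to a contradiction. It does not remove it. Nothing gives Blinding and Primary endpoint precedence over Type of trial. The article does not tie discharge to the recovery criteria. A patient who has been told can influence the discharge day through expectations, and can tell the ward doctor.

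**Conclusion.** The contradiction is established by the text alone, and it bears on whether the primary outcome is decided under masking. The consequence is conditional: if the POD 3 statements are followed, most discharge decisions come after the blind may be broken. The qualitative result rests only on the planned means of 5 and 6 days. The share, roughly 72% to over 99% pooled, rests on an assumed SD of 1 to 3 days and assumed distribution shapes. The 17% and 37% false-positive rates rest further on an SD of 2 and on assumed shifts, so they do not measure bias in this trial.

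Two gaps remain even on the more favourable reading. The dressing may come off before the discharge decision, and the blinding sensitivity analysis is attached to time to functional recovery, not to LOS. That LOS is actually being assessed unblinded cannot be concluded from the article.

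**What to change.** - Reconcile Allocation concealment mechanism, Blinding, Type of trial, Primary endpoint and the Discussion into one rule: allocation is not disclosed to the patient or the ward doctor until the discharge decision is recorded. Keep the exception for medical reasons that Blinding already allows, and leave wound-dressing management to the investigators.
- Ask the blinding-index question of patients and ward doctors before disclosure.
- Run the blinding sensitivity analysis on LOS.
- For patients already discharged, report the unblinding date where it is available, descriptively only. Masked status at discharge depends on LOS itself, since short stays end before the blind can be lifted. Comparing LOS by that status, or restricting the analysis to masked patients, would be confounded by construction.
- If masking to discharge cannot be achieved, state that LOS is largely assessed unblinded and drop the double-blind claim for the primary endpoint.

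The cost is a wording amendment and later disclosure to patients, by about 2 to 3 days on the planned means if disclosure now happens at POD 3. Recruitment began in August 2019, so patients already treated cannot be re-masked, and their unblinding dates may not all be recoverable.
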